### 2.5. Independent Variables

The selection of the parameters (included in the questionnaire) is based largely on the body of evidence from international literature on factors that influence or increase the risks of acquisition of SARS-CoV-2, severe COVID-19 disease, humoral immune response, and perception about vaccines [3,5,9,15,16,18]. Trained research nurses (without any affiliation to the study sites) will measure the height, weight, and mid-upper arm circumference according to standard protocols and the body mass index will be derived.

### 2.6. Validity and Reliability of the Study Instruments

The construct and criterion validity of the instrument have been established by selecting variables that have been used successfully in measuring the outcome measures of this study in multiple studies [3,5,9,15,16,18]. In addition, the instrument has been piloted with five HCWs at one of the study sites and the feedback from the participants was critically reviewed by the investigators, following which adjustments were made in some of the variables. However, the results of the pilot will not be included in the main study.

### 2.7. Blood Sampling

Following aseptic technique, the research nurses will collect up to 5 mL of venous blood in serum separating tube, which will be transported daily to the National Health Laboratory Service (NHLS) for processing. A maximum of three attempts at drawing venous blood samples from the participants per visit will be allowed. If venesection fails after three attempts, the participant will be re-scheduled for another day in order for a doctor (one of the investigators) to draw the blood sample.

For the sub-study (nested cohort study), about 200 participants will be required to attend a follow up during which another round of blood sampling will take place in accordance with standard protocol.

### 2.8. Oropharyngeal Swabs

Participants who report compatible symptoms (fever, cough, sore throat, loss of smell/taste, and shortness of breath) [1] at the time of the study will be offered oropharyngeal swab test for SARS-CoV-2 PCR. This will be captured separately in the research register as well as in the occupational health and safety (OHS) database for follow-up. Where there are gaps, the NHLS database and the Occupational Health Unit’s records will be reviewed for additional data.

### 2.9. Possible Outcomes

SARS-CoV-2 serology results will be matched with the baseline results of SARS-CoV-2 RT-PCR if previously done.

The following categories will emerge:Both SARS-CoV-2 RT-PCR and SARS-CoV-2 serology are positive: COVID-19 diagnosis confirmed, and humoral immune response is present.SARS-CoV-2 RT-PCR is positive but SARS-CoV-2 serology is negative: COVID -19 diagnosis confirmed but there is no persistent humoral immune response or too early for antibody detection.SARS-CoV-2 RT-PCR not done or negative but SARS-CoV-2 serology is positive: COVID-19 diagnosis was missed by PCR but there is a humoral immune response present.Both SARS-CoV-2 RT-PCR and SARS-CoV-2 serology are negative: no confirmed infection with SARS-CoV-2.

All participants will receive their results within a month of the study from designated persons (Occupational Health Champions) at each study site. Additional interventions (clinical consultations and/or psychologist’s or Employee Assistant Programme practitioner’s referral) will be available for HCWs with specific needs.

### 2.10. Nested Cohort Study (N_b_ = 201 Participants)

The sample size for the cohort study was estimated as 201 based on the expected proportion of HCWs (45% was reported in hospital setting in London by Houlihan et al. [2]) who could have acquired SARS-CoV-2 during the peak period of the pandemic. This sample was calculated at a 95% confidence level and confidence interval of 7.5. The final sample was adjusted in anticipation of a 27% attrition rate during the follow-up of the participants.

Only participants in category one will be pooled into the nested cohort study for serial antibody screening at eight-week interval to monitor the rate of decline in the antibody positivity rate (durability of SARS-CoV-2 specific humoral immune response). The participants in this sub-study will have blood samples drawn on two occasions; at baseline and final sample will be drawn at eight-week interval. Most studies have reported significant decline in the antibody levels by three to four months [12,13]. In anticipation of the challenges of follow-up study, participant recruitment will be based on their willingness to allow monitoring of their SARS-CoV-2 antibody levels. There will be no form of coercion of any HCW to participate or continue follow-up. Participants in this sub-study will receive text messages and face-to-face reminders on the date for blood tests.

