## 1. Introduction

Healthcare workers (HCWs) are a high-risk group for severe acute respiratory syndrome Coronavirus-2 (SARS-CoV-2) infection owing to occupational exposure to large numbers of highly infectious patients with COVID-19 disease (mostly pneumonia) requiring hospitalization for supportive oxygen therapy [1]. Despite infection prevention and control (IPC) measures including isolation of cases and the use of personal protective equipment (PPE), HCWs still acquire the infection at a higher rate than the general population. A prospective study of 200 frontline HCWs in London during the peak of viral transmission showed that 44% became infected, more than double that of the local population [2]. A smartphone application survey of almost 100,000 HCWs from the United Kingdom (UK) and United States of America (USA), and over two million members of the general public, with self-reporting of positive reverse transcription-polymerase chain reaction (RT-PCR) for the SARS-CoV-2 infections was performed [3]. It found an almost twelve-fold increased risk (HR = 11.6, 95% CI: 10.9–12.3) of acquiring SARS-CoV-2 among the frontline healthcare workers (HCWs) in comparison with the general population.

In South Africa, HCWs are considered as priority group for daily symptom screening and testing for any potential COVID-19 symptoms [1]. The cumulative prevalence of SARS-CoV-2 infection among HCWs is unknown, given that PCR test is often limited to symptomatic individuals. While this is a source of concern for administrators of the South African Department of Health, it is not clear whether the hazard risk reported by Nguyen et al. [3] is translatable to HCWs in the sub-Saharan African region, where regional risk may vary. There is value in the local seroprevalence testing of HCWs to assess more adequately the extent of SARS-CoV-2 infections (symptomatic and asymptomatic), and to compare this to a group more representative of the community (ante-natal women for the purpose of this study). Such a study was performed in Denmark, where 28,792 HCWs and 4672 blood donors had SARS-CoV-2 IgM/IgG testing. Seroprevalence was higher in HCWs than in blood donors (4.04% vs. 3.04%; risk ratio (RR) 1.33 (95% CI 1.12–1.58); *p* < 0.001). Male HCWs working in the hospitals, and in dedicated COVID-19 wards, were all significant and independent risk factors for the disease [4].

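### The stated inputs do not give a nested cohort of 201, and the 45% used to size it describes the survey, not the cohort

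*Protocol article*

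**What the plan says.** The only sizing rationale for the cohort is in section 2.10 of the protocol article. The number 201 is "based on the expected proportion of HCWs (45% was reported in hospital setting in London". On precision the section states: "This sample was calculated at a 95% confidence level and confidence interval of 7.5". On losses it adds: "The final sample was adjusted in anticipation of a 27% attrition rate during the follow-up of the participants".

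The heading of section 2.10 gives 201 as the cohort size, and section 3.2 compares the baseline serology of the 201 with the eight-week result. So 201 is the number enrolled, before losses. The section mentions neither a finite-population correction nor the formula used to inflate for attrition.

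On entry, section 2.10 says: "Only participants in category one will be pooled into the nested cohort study for serial antibody screening at eight-week interval". Section 2.9 defines category one as positive on both RT-PCR and serology. The declared purpose is to follow the decline in antibody positivity.

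**The concern.** There are two separate problems.

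1. The article prints a complete set of inputs and a result, and they disagree. A reader would take it that 201 enrolled still delivers 7.5 points after 27% have been lost.
2. The planning proportion belongs to another question. The share of workers ever infected is a parameter of the cross-sectional survey. Within the cohort that share is 100% by the entry rule, so precision around 45% does not describe anything the cohort will report.

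Antibody durability is one of the two main outcome domains in section 2.12. What is at stake is whether its stated precision is true and refers to the right quantity.

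**Working it through.** **Inputs (section 2.10):** p = 0.45; z = 1.96; d = 0.075, reading 7.5 as a half-width in percentage points; attrition 0.27; enrolled 201.

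**Attempt to reproduce 201 from the stated inputs**

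- Completers: n = z²p(1−p)/d² = 1.96² × 0.45 × 0.55 / 0.075² = 169.03, so 170.
- Enrolled: 170/(1 − 0.27) = 232.9, so 233. If 169.03 is taken as 169, 169/0.73 = 231.5, so 232.
- Multiplying instead of dividing gives 170 × 1.27 = 215.9, so 216. This is not 201 either.
- Reading 7.5 as the full width of the interval requires about 677 completers, which is further away.

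**What 201 delivers**

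- Completers: 201 × 0.73 = 146.7, about 147.
- Half-width at 45%: 1.96 × √(0.2475/147) = 8.04 points.
- Attrition that 201 can absorb while leaving 170: 1 − 170/201 = 15%.

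**Back-solving with an unstated finite-population correction**, n/(1 + (n − 1)/N):

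| Population N | Completers needed | Inflation | Enrolled | Half-width at 45%, 147 completers |
|---|---|---|---|---|
| 2250 (survey participants) | 157.3, so 158 | × 1.27 | 200.7, so 201 | 7.8 |
| 2250 | 158 | / 0.73 | 216.4, so 217 | 7.8 |
| 1100 | 146.6 | / 0.73 | 200.9, so 201 | 7.49 |
| 1013 (45% of 2250) | 145 | / 0.73 | 198.6, so 199 | 7.44 |

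The half-widths in the last column are 8.04 × √((N − 147)/(N − 1)). With 147 completers the 7.5-point target is met only if N is about 1120 or less.

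**Precision for the proportion losing positivity at eight weeks**, 147 completers, no population correction. The article gives no planning value for this proportion, so a range is shown:

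| True proportion seronegative | 1.96 × √(p(1−p)/147) |
|---|---|
| 10% | 4.85 points |
| 20% | 6.5 points |
| 30% | 7.4 points |
| 50% | 8.1 points (the maximum) |

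The values are the same for 90%, 80% and 70% seronegative.

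**Side note.** The Introduction gives the London figure differently: "A prospective study of 200 frontline HCWs in London during the peak of viral transmission showed that 44% became infected". At 44%, n = 1.96² × 0.44 × 0.56 / 0.075² = 168.3, a difference of about one participant. It has no bearing on the conclusion.

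**The case against.** **A population correction may have been used.** This is the best defence, and it partly stands. A correction on about 1100, followed by the proper division by 0.73, gives 201 and meets 7.5 points. A correction on 1013, the expected number infected among 2250, comes close at 199 and also meets it. A condensed article could have left this detail to the full protocol. But the text as printed states no correction. Table 1 gives 1100 only as one hospital's recruitment figure, and nothing links it to this calculation. The defence therefore shows that 201 could be right, not that it follows from what is written.

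**A reader might infer a specific slip**, namely a correction on 2250 followed by multiplying by 1.27 where dividing by 0.73 was needed. That route does give 201, and it would miss the target. The documents do not support it as the explanation, because it is not the only route and no inflation formula is given.

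**A reader might also infer that the durability sub-study is too small for its purpose.** That does not follow. No hypothesis test, power claim or decision threshold is attached to the 7.5 points. Because 45% is close to the value with the largest variance, using it costs little: for a proportion seronegative of 30% or less, 147 completers do better than 7.5 points.

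**One eight-week proportion is not the whole sub-study.** This is fair. Section 2.12 also names factors associated with durable antibodies, and section 3.2 includes mean duration of persistence. A half-width for one proportion does not justify the size for those.

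**Conclusion.** The point holds in a limited form, and its weight is minor to moderate.

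- **Arithmetic.** As written, the inputs call for about 233 enrolled (232 without rounding up first), not 201. At 45% the half-width after attrition is 8.0 points, against 7.5 stated. With a correction on 2250 it is 7.8. The excess is thus 0.3 to 0.5 of a point, and it disappears if the intended finite population was about 1120 or fewer. The derivation of 201 cannot be recovered from the text.
- **Planning proportion.** The mismatch between 45% and the cohort's endpoint does not depend on any view about population corrections or inflation. It follows from the entry rule in sections 2.9 and 2.10.

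The figures assume the normal-approximation interval for a single proportion under simple random sampling, and losses unrelated to antibody status.

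**What to change.** Keep 201. In section 2.10, remove the 45% infection proportion as the sizing parameter and state the precision of the quantity the cohort reports, for example:

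> 201 participants will be enrolled; with 27% attrition, about 147 will complete. The 95% CI half-width for the proportion seronegative at eight weeks is about 4.85, 6.5, 7.4 and at most 8.1 percentage points for true values of 10%, 20%, 30% and 50%.

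If a finite-population correction was used to reach 201, state it, name its population, and give the attrition formula. The new sentence should be presented as precision for the eight-week proportion only, not as a justification for the other durability outcomes.

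The cost is a change of wording. Recruitment, procedures, analysis and the main survey of 2250 are unaffected. The 7.5-point claim gives way to a range that is better at low rates of antibody loss and slightly worse near 50%.

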## Abstract

Healthcare workers (HCWs) are at increased risk of infection by the virulent severe acute respiratory syndrome coronavirus-2 (SARS-CoV-2). Though data exist on the positivity rate of the SARS-CoV-2 reverse transcription polymerase chain reaction (RT-PCR) test as well as COVID-19-related deaths amongst HCWs in South Africa, the overall infection rate remains underestimated by these indicators. It is also unclear whether the humoral immune response after SARS-CoV-2 infection offers durable protection against reinfection. This study will assess the SARS-CoV-2 seroprevalence amongst HCWs in the Eastern Cape (EC) and examine the longitudinal changes (rate of decay) in the antibody levels after infection in this cohort. Using a multi-stage cluster sampling of healthcare workers in selected health facilities in the EC, a cross-sectional study of 2250 participants will be recruited. In order to assess the community infection rate, 750 antenatal women in the same settings will be recruited. Relevant demographic and clinical characteristics will be obtained by a self-administered questionnaire. A chemiluminescent microparticle immunoassay (CMIA) will be used for the qualitative detection of IgG antibodies against SARS-CoV-2 nucleocapsid protein. A nested cohort study will be conducted by performing eight-weekly antibody assays (X2) from 201 participants who tested positive for both SARS-CoV-2 RT-PCR and serology. Logistic regression models will be fitted to identify the independent risk factors for SARS-CoV-2 infection. The cumulative SARS-CoV-2 infection rate and infection fatality rate among the frontline HCWs will be estimated. In addition, the study will highlight the overall effectiveness of infection prevention and control measures (IPC) per exposure sites/wards at the selected health facilities. Findings will inform the South African Department of Health’s policies on how to protect HCWs better as the country prepares for the second wave of the SARS-CoV pandemic.

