### 2.11. Laboratory Testing

Serum samples will be run on the Abbott ARCHITECT *i*1000SR instrument using the Abbott SARS-CoV-2 IgG assay in accordance with the manufacturer’s instructions. This is a CLIA for the qualitative detection of IgG in human serum or plasma against the SARS-CoV-2 nucleoprotein. Strength of response in relative light units reflects quantity of IgG present and is compared to a calibrator to determine the calculated index (specimen/calibrator [S/C]) for a sample (with positive at 1.4 or greater). This assay was independently evaluated for analytic performance and found to have a specificity of 99.9% from 1020 pre-COVID-19 serum specimens and a sensitivity of 100% at 17 days after symptom onset and 13 days after PCR positivity [19].

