### 3.2. Sub-Analysis (Longitudinal Changes in Antibody Detection)

Baseline detection of SARS-CoV-2 specific antibodies (IgG) will be summarized using descriptive statistics (counts and proportions for categorical data). HCWs with confirmed diagnosis with SARS-CoV-2 RT-PCR will be evaluated for the presence or absence of antibodies and the time interval between the two tests will be estimated. Durability of SARS-CoV-2 specific IgG antibodies will be assessed first by estimating the frequency (percentage) of the presence of antibodies and the mean (standard deviation) duration of persistence of the antibodies. Presence or absence of SARS-CoV-2 specific antibodies (IgG) (yes/no) at baseline will also be correlated with the disease severity.

Further, the nested cohort study will also provide additional answers regarding the durability of the humoral immune response. Baseline serology results of the 201 participants in the sub-study will be compared with the results of the subsequent serology test done at eight-week interval.

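### The stated aim is the rate of decay in antibody levels, but the nested cohort is defined on positivity, and the S/C index that could measure decay is assigned to no outcome.

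*Protocol article*

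**What the plan says.** - **Aim (Abstract).** The study will "examine the longitudinal changes (rate of decay) in the antibody levels after infection in this cohort". This is a quantitative target.
- **Purpose of the cohort (section 2.10).** Serial testing is done "to monitor the rate of decline in the antibody positivity rate". This is a binary target. The same section also speaks of levels, both when it justifies the timing and when it describes what participants agree to have monitored.
- **Entry and sampling (sections 2.9 and 2.10).** Only people positive on both RT-PCR and serology enter. Each gives two samples, eight weeks apart.
- **Assay (section 2.11).** The test is described as qualitative, positive at S/C of 1.4 or more. The section adds: "Strength of response in relative light units reflects quantity of IgG present". An S/C index is calculated for each sample.
- **Analysis (section 3.2).** Baseline detection "will be summarized using descriptive statistics (counts and proportions for categorical data". For RT-PCR-confirmed workers, durability is assessed by "estimating the frequency (percentage) of the presence of antibodies and the mean (standard deviation) duration of persistence of the antibodies". A yes/no variable at baseline is related to disease severity. For the cohort itself, baseline serology results "will be compared with the results of the subsequent serology test done at eight-week interval"; neither scale nor method is given.
- **Main outcomes (section 2.12).** One of them is the set of factors associated with durable IgG.

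**The concern.** A decay rate in levels and a fall in the proportion positive are different estimands, and the article gives one as the aim and the other as the cohort's purpose. The cohort is 100% positive at baseline by design, so the paired binary comparison can move in one direction only. It reduces to the share who fall below 1.4 by eight weeks. Two groups with the same decay rate but different starting S/C would show different shares.

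At stake are a headline aim, which the defined endpoint would not deliver, and information on factors for durability. On the binary scale, someone whose index falls a long way but stays above 1.4 looks the same as someone whose index does not move.

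**Working it through.** **1. The plan's cohort size.** Inputs from section 2.10: 45% expected, 95% confidence, half-width 7.5 points, 27% attrition.

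- n0 = 1.96² × 0.45 × 0.55 / 0.075² = 169.02.
- Assuming a finite-population correction with N = 2250 (not stated there): 169.02 / (1 + 168.02/2250) = 157.28, rounded up to 158.
- 158 × 1.27 = 200.7, rounded up to 201. The figure reproduces.

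This size targets the precision of an infection proportion, not of a decay or seroreversion rate. With 27% lost, 201 × 0.73 = 146.7, about 147 completers.

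**2. What positivity hides at the cited half-life.** Inputs: 36 days (Introduction), 56 days between samples (2.10), cut-off 1.4 (2.11). Assumption: S/C is proportional to IgG, which the article does not state.

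- Fold fall = 2^(56/36) = 2.94; loss = 1 − 1/2.94 = 66%.
- Starting value that just reaches the cut-off = 1.4 × 2.94 = 4.12.

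Anyone starting above about 4.1 is still scored positive.

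**3. Same decay, different seroreversion.** Simulated share below 1.4 at 56 days. All inputs other than the 36-day half-life are assumed: baseline log S/C normal with SD 0.6, cut at 1.4; SD of within-person log change 0.3 to 0.5. Noise is added to the follow-up value only, so regression to the mean is not modelled.

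| Half-life (days) | Median baseline S/C 3 | Median baseline S/C 5 |
|---|---|---|
| 36 | 62–65% | 38–39% |
| 72 | 30–33% | 12–16% |
| 120 | 18–22% | 6–10% |

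A half-life of 120 days with median 3 gives more seroreverters (18–22%) than a half-life of 72 days with median 5 (12–16%). The binary endpoint can therefore rank slower decay as the less durable response.

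**4. Number of seroreverters among 147.** The article gives no rate. At 10%: 14.7, about 15. At 38%: 55.9, about 56. At 65%: 95.6, about 96. The low figure does not belong with a 36-day half-life; in the table, about 10% appears only at 120 days with median 5.

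**5. What the paired log change offers.** The 95% half-width of the mean log change is 1.96 × SD/√147. For SD 0.3, 0.5 and 0.8 (assumed) this is 0.048, 0.081 and 0.129, so the geometric mean ratio is known to within about 5%, 8% and 14%.

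For a factor splitting completers 73 against 73, with assumed half-lives of 72 and 120 days, the difference in log change is ln 2 × 56 × (1/72 − 1/120) = 0.216.

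| SD of log change | Power on log S/C | Power on positivity |
|---|---|---|
| 0.5 | 74% | 19–29% |
| 0.8 | 37% | 15–18% |

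The size of the gain depends on the SD; its direction is the same in both cases.

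**The case against.** **The plan may not discard the index.** A reader might infer that the cohort analysis uses only yes/no results and throws the S/C value away. The article does not say so. The counts and proportions in section 3.2 describe baseline detection. The yes/no variable is also tied to baseline: "Presence or absence of SARS-CoV-2 specific antibodies (IgG) (yes/no) at baseline will also be correlated with the disease severity". The cohort's own sentence names no scale, and a fuller protocol or analysis plan may specify S/C. This stands, and it limits the point to a conflict between aim and stated purpose, with an index left unassigned. It does not remove the conflict, because section 2.10 itself names positivity.

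**Few events.** A reader might also infer that seroreverters will be too few to study. No rate in the article supports that, and at the cited half-life they could be numerous.

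**Persistence of positivity is a legitimate endpoint, and the assay is called qualitative.** Both are true. Seroreversion is then a defensible aim, but it is not the aim in the abstract. Nor does the planned mean duration of persistence fill the gap: with two samples, loss is known only to fall within an eight-week window or not to have happened yet.

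**A log-scale analysis has limits of its own.** The Introduction cites a large study in which levels rose to two months and then held, so one log-linear decline from the PCR date could be wrong for recent infections. Selection at 1.4 leaves some regression to the mean on either scale. The assay behind the cited 36-day half-life is not stated, so a half-life from this index would not be directly comparable with it. These limits stand and shape the fix.

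**Conclusion.** The point holds as a mismatch of estimands. The abstract aims at decay in levels, section 2.10 defines the cohort by positivity, and nothing assigns the S/C index to an outcome. With everyone positive at entry, the positivity endpoint is a single seroreversion proportion that cannot identify a decay rate. That conclusion follows from the entry rule alone and needs no assumed figure.

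The size is illustrative. The 66% loss and the 4.1 threshold rest on S/C being proportional to IgG and on the cited half-life. The seroreversion shares and the power figures rest on assumed baseline distributions and SDs.

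It would go too far to say that the sub-study can never estimate decay: if the unspecified eight-week comparison is made on S/C, it can estimate change. The cross-sectional seroprevalence analysis is unaffected. This should be settled before the follow-up results are analysed.

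**What to change.** - Export the S/C value with each qualitative result.
- Make the within-person change in log S/C, over the actual interval between the two samples, the main cohort outcome, with a 95% CI.
- Relate it to severity, age, sex and comorbidity, with time since PCR positivity as an adjustment or interaction, so that participants whose levels may still be rising are not forced into one log-linear decay.
- Keep the proportion at or above 1.4 as a secondary outcome, with a sensitivity analysis for baseline values near the cut-off.
- Name the scale and method of the cohort comparison in section 3.2, and align the abstract with section 2.10.
- If only seroreversion is wanted, restate the aim in the abstract instead.

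**Cost:** one extra exported field and a few sentences; no extra visits, blood or participants. **Downside:** the index is semi-quantitative, so any half-life is assay-specific and must be labelled so.

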Areas of uncertainty with SARS-CoV-2 antibody testing, is how long the IgG antibody levels remain detectable in the blood and the durability of humoral immune response post-infection. Early reports of serial antibody testing in recovering COVID-19 cases indicated an apparently short-lived antibody response. One study of 34 mild cases reported a half-life of 36 days for IgG levels measured over approximately 90 days [12]. In contrast, a recent seroprevalence study was performed on over 30,000 Icelanders, including 1797 RT-PCR confirmed COVID-19 cases, using six different antibody assays. This study demonstrated good IgG antibody durability, with levels rising to two months post-infection, and then sustained up to four months (the study cut-off) [13]. It is therefore unclear whether there are regional or ethnic variations in the durability of SARS-CoV-2 antibodies. The proposed study aims to estimate the cumulative SARS-CoV-2 infection rate and will further examine the durability of the humoral immune response specific to this virus in a cohort of HCWs in the Eastern Cape, South Africa.

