### 2.2. Participants

The study population will include all categories of HCWs at the selected health facilities. Given the large number of HCWs (doctors, nurses, allied health workers, and administrative staff) in the regional (about 1400 staff) and tertiary (about 1500 staff) hospitals in comparison to those in the primary health care (about 120 staff), it is expected that the majority of the participants in this study will be recruited from the two large hospitals. Since this cross-sectional study aims to provide mass screening (using a SARS-CoV-2 serological test) for all HCWs, about 2250 HCWs are expected to take part in this study. The estimated number of participants per study site is proportional to the overall count of HCWs at each site. A total of 750 antenatal women will be recruited from the study sites to provide data on the community infection rate. The recruitment of HCWs is pre-stratified for inclusivity and is proportionate to the total head count of staff in each facility as shown in Table 1.

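### The nested cohort's eight-week comparison is not tied to time since infection, and section 2.10 and the Introduction describe reference 13 incompatibly

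*Protocol article*

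**What the plan says.** All references are to the protocol article.

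- **Entry.** Section 2.10 takes only category-one workers, defined in 2.9 as positive on both RT-PCR and serology. It sets no lower or upper limit on time since infection or since the PCR.
- **Sampling.** Section 2.10 plans two samples per participant, at baseline and eight weeks later.
- **Aim.** Section 2.10 aims at the decline in antibody positivity. The Abstract aims at the decay of antibody levels following infection.
- **Cited evidence.** Section 2.10 states "Most studies have reported significant decline in the antibody levels by three to four months [12,13". The Introduction describes reference 12 as 34 mild cases with an IgG half-life of 36 days over roughly 90 days. It then contrasts this with reference 13, which showed "levels rising to two months post-infection, and then sustained up to four months (the study cut-off) [13". It leaves the durability question open.
- **Analysis.** Section 3.2 will estimate the interval between PCR and serology in PCR-confirmed workers. For the 201 cohort members it says only that the baseline results "will be compared with the results of the subsequent serology test done at eight-week interval". It does not say that the interval enters this comparison.

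**The concern.** There are two linked problems.

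First, 2.10 cites reference 13 for a decline by three to four months, while the Introduction says the same study found no decline up to four months. Section 2.10 therefore treats as settled the question that the Introduction presents as open.

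Second, follow-up starts at enrolment, not at a fixed time after infection. Recent and older infections can both enter. Section 2.8 offers a PCR to people with symptoms at the study visit, and 2.11 reports full assay sensitivity at 17 days after symptom onset, so someone a few weeks past infection can qualify. Recruiting the sites concurrently (2.3) aligns calendar time, not time since infection. A change measured from such a starting point partly reflects when participants happened to be infected. A cohort with many recent infections could look more durable than one with many old infections, even if the underlying antibody course were the same.

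**Working it through.** **Inputs.** Cohort 201, expected proportion 45%, half-width 7.5 points at 95% confidence, attrition 27% (2.10); 2250 workers (2.2); 56 days between samples (2.10); half-life 36 days for reference 12, and a rise to two months then a plateau to four months for reference 13 (Introduction); positivity at an S/C index of 1.4 or more (2.11).

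**1. The plan's own figure.**
- n0 = 1.96² × 0.45 × 0.55 / 0.075² = 169.02.
- With a finite-population correction to 2250: 169.02 / (1 + 168.02/2250) = 157.3, rounded up to 158.
- 158 × 1.27 = 200.7, so 201 is reproduced, but only with a correction that the text does not state. Without it, 170 becomes 216 (× 1.27) or 233 (÷ 0.73).
- The present point does not depend on how 201 was reached. What matters here is the expected number of completers: 201 × 0.73 = 146.7, about 147.

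**2. What each source implies over 56 days.**
- Reference 12: 0.5^(56/36) = 0.340, so 34% of the baseline level remains.
- Reference 13: a ratio of 1.0 or more up to month four, and above 1.0 for the part of follow-up that falls before month two.

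**3. Where time since infection enters.**
- *Levels, reference 13's pattern.* With two months read as 60 days, someone enrolled at day 20 would be rising for 60 − 20 = 40 of the 56 days. Someone enrolled at day 60 would be flat. The paired change differs by enrolment time alone.
- *Levels, reference 12's pattern.* A constant half-life gives the same ratio whenever a person enrols, so levels would not be affected.
- *Loss of positivity, reference 12's pattern.* A baseline S/C below 1.4 / 0.340 = 4.12 falls under the cut-off within 56 days. A person enrolled at an S/C between 4.12 and 8.23 (2 × 4.115) stays positive. The same person enrolled 36 days later would start between 2.06 and 4.12, still be eligible, and lose positivity. So this measure depends on time since infection even under a single decay rate.

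**4. Reach of follow-up.** To give a sample at day 90 or day 120 after infection, a participant must enrol no earlier than day 90 − 56 = 34 or day 120 − 56 = 64.

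**5. Illustration of mixing (assumed shares).** Suppose a share w falls with a 36-day half-life and the rest stay flat. The pooled geometric-mean ratio is 0.340^w and the apparent half-life is 36/w days.

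| Share falling | Ratio at 56 days | Apparent half-life (days) |
|---|---|---|
| 100% | 0.34 | 36 |
| 75% | 0.45 | 48 |
| 50% | 0.58 | 72 |
| 25% | 0.76 | 144 |

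These shares are not estimates; the documents give nothing from which to estimate them.

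**The case against.** Several stronger readings are tempting, and the documents do not support them.

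- *That the cohort cannot measure decay.* Every member has a positive PCR, 3.2 already plans to estimate the PCR-to-serology interval, and the assay yields an S/C index. Paired change by time since PCR can be computed. The gap is in the stated comparison, not in the data.
- *That the study could not tell the two published patterns apart.* If everyone followed one source or the other, a ratio of 0.34 against 1.0 or more would separate them clearly. The spread in the table needs both patterns to be present at once, which neither source is said to show.
- *That the eight-week interval rests on the disputed citation.* Section 2.10 does not say so. The link is inferred from the sentence's position, and three to four months does not yield eight weeks.
- *That 2.10 is the section in error.* The cited studies are not at hand. The documents show a conflict, not which side is right.

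It can also be argued that mixing may be slight: the Abstract places the study before a second wave and 2.10 refers to infections in the peak period, so many may be old. And 2.10 states its aim as loss of positivity, where a rise and a plateau both count as still positive, so rises do not offset falls as they do for levels. Both points are fair. They limit the size of the problem without removing it, since loss of positivity also varies with time since infection (step 3).

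Finally, a condensed article may leave the choice of bands to a fuller document. That excuses missing detail. It does not excuse two incompatible accounts of one source, or a stated comparison with no time origin when the aim is decay after infection.

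**Conclusion.** The point holds in a limited form. The Introduction and section 2.10 cannot both be right about reference 13; as the Introduction stands, only reference 12, with 34 mild cases, supports early decline. The baseline-versus-eight-week comparison, as stated, gives a result that depends partly on participants' time since infection, and so does not isolate decay after infection.

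The size of that dependence is unknown, because the documents give no distribution of time since infection. The figures 0.34 and 1.0 or more mark how far apart the two cited patterns are over 56 days; they do not estimate bias. They assume that the Introduction's descriptions are accurate. They do not extend past about 90 days for reference 12 or four months for reference 13.

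**What to change.** - **Reconcile the Introduction and 2.10 on reference 13**, after checking the source. If the Introduction is correct, cite only reference 12 for early decline in 2.10.
- **Amend 3.2** so that the paired eight-week change is analysed by days since first positive PCR, as a covariate or as the time axis, and is also reported in bands fixed before the follow-up results are seen. Do this for both the S/C index and loss of positivity at 1.4. Keep the overall figure alongside.
- **Do not restrict the decline estimate to participants at 60 days or more after PCR.** That threshold assumes reference 13's pattern; if reference 12's holds, it discards people already declining.
- **State a limitation.** Entry requires current seropositivity, so participants enrolled late after infection are selected for slower decline. Banding shows this selection but does not remove it.

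**Cost.** Wording and analysis only: no extra visits or samples, and the PCR-to-serology interval is already planned. The downside is precision within bands. For example, with 147 completers and an assumed 20% losing positivity, the 95% half-width is 1.96 × √(0.2 × 0.8/147) = 6.5 points overall. In each of three equal bands of 49 (also an assumption) it is 1.96 × √(0.2 × 0.8/49) = 11.2 points. Using days since PCR as a continuous covariate avoids splitting the sample.
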